## Introduction

### Background

According to sociodemographic trends, it is estimated that at least 23.3% of German residents will be over 67 years old in 2030 [1]. The absolute number of German residents over the age of 80 years is expected to increase from 4.4 million in 2013 to more than 9 million in 2060 [1]; this projected figure corresponds to approximately 12–13% of future population estimates. Rising morbidity and health care costs among German’s elderly population are also expected [2].

Current estimates of need suggest that 40.7–96.1% of dying people could benefit from palliative care. An analysis of all deaths in 2013 in Germany found an estimated need of 78% across all age groups [2]. In general, approximately 80–90% of people requiring palliative care can be adequately cared for through generalist outpatient palliative care (level 1) [2]. The European Association for Palliative Care (EAPC) white paper on standards and norms for hospice and palliative care in Europe states: ‘Whereas a palliative care approach will provide adequate care for many of these patients, it has been estimated that at least 20% of cancer patients and 5% of non-cancer patients require specialist palliative care in the last year of their life’ [3]. Although palliative care offerings in Germany have recently expanded and the number of service providers has increased, there is still a great need for palliative care, especially in rural areas [4].

In Germany, outpatient and inpatient palliative care has undergone very dynamic development to respond to sociodemographic changes and palliative care needs. Important milestones in the political effort to improve palliative care in Germany have included the introduction of specialist outpatient palliative care (level 3) in the Social Code Book V (SGB V) in 2007 [5]; the inclusion of palliative care within the statutory health insurance system of general patient care in the Hospice and Palliative Care Act of December 2015 [6]; and the expansion of the Uniform Value Scale (‘Einheitlicher Bewertungsmaßstab’, EBM) to include generalist outpatient palliative care (level 1) by general practitioners (GPs) in 2013 [4, 7]. In 2016, during the implementation of the Hospice and Palliative Care Act, an agreement was reached for the establishment of an intermediate level of generalist outpatient palliative care (level 2) [8, 9].

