### Study phases and data collection

In phase 1, work package 1a, quantitative routinely collected data from the statutory health insurance provider Allgemeine Ortskrankenkassen Lower Saxony (AOKN) will be used to analyse the development of level 2 outpatient palliative care services over time and to identify patients who died in 2019 and received outpatient palliative care services (at any level). Sociodemographic and disease-related data for these patients will be collected and compared according to those who received level 2 palliative care versus those who received palliative care at levels 1 or 3. The consortium will reveal the care trajectories of these patients, the patients who received different forms of outpatient palliative care and the transitions that occurred between levels of outpatient palliative care. In addition, the use of health care services beyond palliative care (but alongside level 2 palliative care) will be examined from billing records; such services might include medical specialists or hospital admissions. These data are expected to reveal the extent to which level 2 palliative care is implemented. Finally, a comparison with data from patients deceased in 2017 will show on a macro level whether (and to what extent) the introduction of level 2 palliative care shifted the type and administration of palliative care at levels 1 or 3. The data required for this will be extracted and analysed by the AOKN.

In phase 1, work package 1b, a quantitative, standardised questionnaire for GPs will be developed on the basis of the literature, previous scientific findings, available political statements and contributions from relevant professional associations. The online survey will be sent to all (N = 5,158) GPs registered in Lower Saxony to collect information on the number and characteristics of physicians offering level 2 palliative care. A response rate of approximately 15% (n = 774) is expected.

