### Study population

The main target groups for analysis will be:

AOKN members who died in 2019;health care providers and experts at the micro level, including GPs; oncologists; pain medicine or palliative care specialists; geriatricians; and multi-disciplinary specialists from level 3 outpatient palliative care teams, nursing care services, nursing care facilities and inpatient hospices; andpalliative and hospice care stakeholders at the meso and macro levels, including representatives from the German Hospice and Palliative Care Association (Deutscher Hospiz- und Palliativverband), the German Association for Palliative Medicine (Deutsche Gesellschaft für Palliativmedizin), the Professional Association of specialised outpatient palliative care (Fachverband SAPV), other societies and professional associations, the Association of Statutory Health Insurance Physicians Lower Saxony (Kassenärztliche Vereinigung Niedersachsen), GP associations, the German Home Care and Nursing Society (Deutscher Pflegeverband e.V.), and health care insurance providers.

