### Data analysis

The data analysis will aim at describing the current state of level 2 outpatient palliative care administration, in practice, and determining consented recommendations for its optimisation and development. The analysis of secondary data from the AOKN in phase 1, work package 1a, will be carried out quantitatively and descriptively. Quantitative data from the surveys with GPs and specialist outpatient palliative care teams in work packages 1b and 1c will also be analysed descriptively, using IBM SPSS Statistics version 25 (SPSS Inc., Chicago, IL, USA).

Qualitative data from the expert workshop in phase 2, work package 2a, will be transcribed verbatim from the audio record by student assistants, and analysed qualitatively in MaxQDA (VERBI Software Consult Sozialforschung GmbH, 1989–2020), using the methodological principles of qualitative content analysis [13, 14]. The thematic characteristics of level 2 palliative care determined in previous study phases will comprise an a priori category system, which will be successively expanded with the workshop data.

Quantitative data from phase 2, work package 2b, will be processed in IBM SPSS Statistics 26 (SPSS Inc., Chicago, IL, USA). Recommendations from the first Delphi round that receive support from at least 80% of the participants (on the basis of the scale responses “I rather agree” and “I fully agree”) will be considered consented. Results will be calculated by means of a frequency analysis. Recommendations that are non-consented in Delphi round 1 will be revised according to any free text comments and subjected to a second Delphi round. This interim analysis and adaptation of the recommendations will take approximately 2–3 weeks. Following this, the revised recommendations will be sent to all participants who completed the first Delphi round for a second online evaluation. A third round will be applied, if necessary, following the same method.

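### The 2017 to 2019 change in level 1 and level 3 care is attributed to level 2 with no stated account of case mix, and patient characteristics are specified only for 2019 recipients

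*Protocol article*

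**What the plan says.** The section on study phases and data collection sets out two comparisons for work package 1a.

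- **Between care levels, 2019 deaths only.** The insurer's data are used to "identify patients who died in 2019 and received outpatient palliative care services (at any level"). The next sentence reads "Sociodemographic and disease-related data for these patients will be collected and compared", and the contrast is level 2 recipients against level 1 or level 3 recipients.
- **Between years.** The paragraph then says that "a comparison with data from patients deceased in 2017 will show on a macro level whether (and to what extent") a shift took place, and it names the cause in the same sentence: "the introduction of level 2 palliative care shifted the type and administration of palliative care at levels 1 or 3". On the data for this it says only: "The data required for this will be extracted and analysed by the AOKN".

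The data analysis section says that the work package 1a analysis "will be carried out quantitatively and descriptively". The study population section lists "AOKN members who died in 2019" as the insured target group and does not mention 2017 deaths. The inclusion criteria for deceased patients (adults, continuously insured in the year of death and the calendar year before) are not limited to 2019. The background section cites a European white paper by which "at least 20% of cancer patients and 5% of non-cancer patients require specialist palliative care" in the last year of life.

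**The concern.** The sentence on the 2017 comparison promises two things from a two-year contrast: that there was a shift, with its size, and that the introduction of level 2 caused it. The stated method supports neither without further steps.

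The use of each level is likely to depend on diagnosis and probably on age. The difference between the two years then mixes a change in who died with a change in how similar patients were cared for. Only the second is a shift between levels. The article does not say how the two will be separated, and it ties patient characteristics to one of the two years.

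The result is meant to be used. Phase 1 findings go to the expert workshop and the Delphi survey, and the article expects the recommendations to inform legislation. A stated extent of shift that contains a case-mix component would travel along that route.

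**Working it through.** The article gives no rate, sample size or effect for the year comparison, so there is no figure of the plan to reproduce. The check has two parts.

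**1. What is stated for each year**

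| Item | 2019 decedents | 2017 decedents |
|---|---|---|
| Listed as target group | yes | no |
| Age and insurance criteria | apply | apply (no year given) |
| Patient characteristics | specified, for recipients of outpatient palliative care | left open (whatever is required) |
| Stated use of characteristics | comparison between care levels | none stated |
| Handling of case mix between years | none stated | none stated |

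**2. Illustration of a pure case-mix change**

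Inputs:
- Specialist need is 20% in cancer and 5% in non-cancer (background section). These are floor estimates of need, used here only for the size of the gap.
- The cancer share *c* among all eligible decedents is assumed to be 20%, 25% or 30%. The document gives none.
- The change in *c* from 2017 to 2019 is assumed to be 1 to 10 points. The document gives none.
- Care within each diagnosis group does not change.

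Expected need in percent = 20*c* + 5(1 − *c*) = 5 + 15*c*. The slope is therefore 0.15 points per 1-point change in cancer share, in either direction.

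| Assumed starting share | Starting need | 1-point change | 2 points | 5 points | 10 points |
|---|---|---|---|---|---|
| 20% | 5 + 15 × 0.20 = 8.00% | 0.15 (1.9%) | 0.30 (3.8%) | 0.75 (9.4%) | 1.50 (18.8%) |
| 25% | 5 + 15 × 0.25 = 8.75% | 0.15 (1.7%) | 0.30 (3.4%) | 0.75 (8.6%) | 1.50 (17.1%) |
| 30% | 5 + 15 × 0.30 = 9.50% | 0.15 (1.6%) | 0.30 (3.2%) | 0.75 (7.9%) | 1.50 (15.8%) |

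Cells give the change in points, with the change relative to starting need in brackets.

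Example: a rise in cancer share from 25% to 30% moves the crude figure from 8.75% to 9.50%, and a fall from 25% to 20% moves it to 8.00%. Nobody is treated differently in either case. Directly standardised to the 30% mix, both years give 0.30 × 20 + 0.70 × 5 = 9.50%, a difference of 0.

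The result depends on the gap between the diagnosis groups. With assumed rates of 40% and 5% the slope is 0.35 points per point of cancer share, so a 1- to 10-point change moves the crude figure by 0.35 to 3.5 points.

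**The case against.** The strongest reply is that this is a condensed article. Variable lists and adjustment methods belong in the full protocol or analysis plan. Stratified and directly standardised proportions are themselves descriptive statistics, so the proposed analysis already fits the stated method.

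Much of this stands, and it rules out several stronger readings that a reader might infer:

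- **That the comparison is planned as crude.** The article does not say so. It only states no handling of case mix.
- **That the 2017 data will lack case-mix variables, so that standardisation would be impossible.** The article leaves the 2017 fields open. The insurer extracts and analyses its own data, the abstract speaks of 2017–2019, and the adult criterion means that age at death must be known for any decedent included.
- **That age, sex and diagnosis are specified for 2019.** Only two generic classes of characteristics are named.
- **That the bias is known to be large.** The 20% and 5% describe need among all patients in the last year of life, not use of level 3 in Germany. They cannot be carried over to people already receiving outpatient palliative care, which is a different denominator. The ageing figures in the background section run to 2030 and 2060 and say nothing about two years within one insurer.

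A further objection concerns the remedy. Level 2 was created for people under-served at level 1 but not suited to level 3. A changed mix of *recipients* may therefore be an effect of level 2, and standardising among recipients could remove it. This is correct, and it is why the denominator must be all eligible decedents.

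What the reply does not meet is the attribution. That is a statement in the article itself, and it goes beyond the method that the article gives. The scope of the 2017 extract is also best settled before the insurer runs it.

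**Conclusion.** The point holds in limited form. The article attributes the 2017 to 2019 difference in level 1 and level 3 care, and its extent, to level 2. It states only a descriptive method and no account of case mix between the years, and it specifies patient characteristics only for the 2019 recipients. A change in who died could be read as a shift in care.

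The size is illustrative: 0.15 points of expected specialist need per point of cancer share, given the article's need figures and unchanged care within diagnosis groups. If the cancer share moved by only a point or so, the artefact is minor.

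Standardisation would not justify the causal wording either. It removes differences in the measured characteristics only. Other changes over the two years remain, and the study aims section dates the first implementation of level 2 to 2017, so the comparison year is not a clean period before introduction.

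**What to change.** 1. State that the insurer extracts the same social and disease-related fields for all eligible decedents of 2017 and of 2019, and name the 2017 decedents in the study population section.
2. Report the proportion of all eligible decedents, not only of recipients, who used each level in each year. Give it crude and directly standardised to one common distribution (for example that of the 2019 decedents) of age band, sex and cancer versus non-cancer.
3. Base statements about a shift on the standardised figures.
4. Word them as a change between 2017 and 2019, not as the effect of introducing level 2, and say that other time trends and the 2017 introduction year limit the reading.

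The cost is slightly more extraction and one extra table by the insurer's analysts. The estimated shift may become smaller or larger. It would grow, for instance, if the cancer share rose while similar patients were cared for less often at level 3, since the two changes offset each other in the crude figure.

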In phase 1, work package 1c, comparable to work package 1b, a quantitative, standardised online questionnaire for teams providing specialist outpatient palliative care (level 3) will be developed. The questionnaire will aim at quantifying respondents’ experiences with working at the interface of level 2 and level 3 palliative care. It will also seek to ascertain how work at the interfaces between palliative care levels 1, 2 and 3 does or does not succeed in practice, and which practical implementation models for level 2 have been developed. The questionnaire will be sent to all (N = 59) registered specialist outpatient palliative care teams in Lower Saxony, and a response rate of approximately 50% (n = 30) is expected.

In phase 2, work package 2a, the results from phases 1a–c will be presented and discussed in an expert workshop at Hannover Medical School. The discussion will aim at developing ideas to adapt and optimise level 2 outpatient palliative care. Approximately n = 20 care providers and stakeholders from hospice and palliative care in Germany will participate in the expert workshop. A drop-out rate of 10% due to illness, other commitments and personal reasons is expected. Personal invitations will be sent out until the target number of N = 22 experts is reached. The result of the work package 2a will be initial formulations of possible recommendations, which will be subjected to further scrutiny in work package 2b.

In phase 2, work package 2b, the empirically derived recommendations from phases 1 and 2a will be agreed upon via a multi-round Delphi survey [12] involving n = 40 experts with sufficient influence to promote the project results and recommendations nationally, including participants from phase 2a. To compensate for an expected participation rate of 20–30% and a drop-out rate of 10%, approximately N = 120 experts will be invited. Delphi survey data will be collected with the aid of an online tool. Participants will be asked to indicate their level of agreement with each individual recommendation on a 4-point Likert scale, with regards to relevance, clarity and feasibility. Free text fields will also be included for participants to provide additional comments on the recommendations.

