## Discussion

### Study risks

Access to health care providers and stakeholders in the field of hospice and palliative care can be difficult, depending on the attitudes and experiences of these parties with respect to scientific research. Thus, recruiting the intended number of participants in phase 1, work packages 1b and 1c, and phase 2, work packages 2a and 2b, may be methodologically difficult. However, there are several reasons to predict the successful application of the various work packages: 1) participation will require only a single (questionnaire, expert workshop) or a few short (Delphi survey) expenditures of time; 2) the target populations are not difficult to reach; 3) the target number of participants was calculated in accordance with the topics and research methods applied in the respective study phases; and 4) recruitment will take place throughout Lower Saxony in phase 1 and Germany in phase 2.

To achieve the target sample sizes, the project team will take the following actions, if necessary:

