Phase 1:All registered GPs in phase 1, work package 1b, will be informed about the project and invited to participate in the survey, primarily via email and secondarily via letter or fax, if no email address is available.The survey invitation will be advertised in the ‘Ärzteblatt’ Lower Saxony, which is distributed to all registered physicians in Lower Saxony. GPs on existing mailing lists (e.g. for teaching practices at the Hannover Medical School) will also be contacted.All specialised palliative care teams in phase 1, work package 1c, will be informed about the project and invited to participate in the online survey via email or, in exceptional cases, via letter.The online questionnaires for work packages 1b and 1c will be accessible for at least 4 weeks, with weekly reminders sent via email.Phase 2:To encourage participation in the planned expert workshop in phase 2, work package 2a, participants will be compensated for their loss of working hours, travel costs to and from the workshop and overnight accommodation.To compensate for a possible low participation rate of 20–30% and an expected drop-out rate of 10% during the Delphi survey in phase 2, work package 2b, as many potential participants as possible will be informed and invited to participate.It is assumed that, based on their experiences with palliative care and health services research, participating health care providers and stakeholders will have a high intrinsic motivation to improve palliative care.The project team will respond to challenges in a timely manner, organising additional conference calls and project meetings, as needed.

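### The Delphi invitation figure of about 120 does not follow from the stated participation rate, drop-out rate and target of 40 experts

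*Protocol article*

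**What the plan says.** The Protocol article, under Study phases and data collection, describes work package 2b as a multi-round Delphi survey "involving n = 40 experts with sufficient influence to promote the project results and recommendations nationally, including participants from phase 2a". The next sentence gives the recruitment reasoning: "To compensate for an expected participation rate of 20–30% and a drop-out rate of 10%, approximately N = 120 experts will be invited". The figure of 120 is therefore presented as the number that offsets the two rates.

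The experts from work package 2a come from the workshop described just before: "Approximately n = 20 care providers and stakeholders from hospice and palliative care in Germany will participate in the expert workshop". The article gives no separate Delphi participation rate for them, and does not say whether they are among the 120 or additional to it.

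Under Study risks, the article lists calculated target numbers among its reasons to expect successful recruitment: "the target number of participants was calculated in accordance with the topics and research methods applied in the respective study phases". It then lists actions to be taken if needed to reach the targets. For the Delphi, "as many potential participants as possible will be informed and invited to participate". That list repeats both rates, but describes 20–30% as a possible low rate. Study phases and data collection gives the same range as the rate expected.

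Under Data analysis, a recommendation counts as consented at 80% support, and the second round goes only to those who completed the first.

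**The concern.** The sentence claims to compensate for low uptake and attrition, yet 30% of 120 is already below 40 before anyone drops out. A reader who takes the article at its word would expect 40 panellists and would, on its own rates, get far fewer.

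The Delphi settles the recommendations, one of the project's two main expected results. Later rounds draw only on first-round completers and the article describes no replacement, so a thin first round carries through. The article also wants inpatient, ambulatory, generalist and specialist providers, and all interfaces with level 2 care, adequately represented. That is harder with 22 to 32 people than with 40. One vote is worth 2.5 percentage points in a panel of 40 (1/40), 3.1 in a panel of 32 (1/32) and 4.5 in a panel of 22 (1/22), so the 80% threshold becomes coarser.

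**Working it through.** **Inputs** (all from Study phases and data collection): target 40; invitations about 120; participation 20–30%; drop-out 10%; workshop attendance about 20.

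**Do the article's other recruitment figures reproduce?** Yes:
- GP survey: 5,158 × 0.15 = 773.7, stated as 774.
- Specialist teams: 59 × 0.50 = 29.5, stated as 30.
- Workshop: 22 × 0.90 = 19.8, stated as about 20.

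So the article normally applies its rates in the plain way, and the Delphi figure is the exception.

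**Forward check.** Starters = 120 × participation; completers = starters × 0.90.

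| Participation | Starters | Completers | Shortfall of completers against 40 |
|---|---|---|---|
| 20% | 24 | 21.6 | 18.4 |
| 25% | 30 | 27.0 | 13.0 |
| 30% | 36 | 32.4 | 7.6 |

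The article does not say whether 40 means starters or completers. Neither reading reaches it.

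**Implied participation.** For 40 completers: 40 / (120 × 0.90) = 37.0%. For 40 with drop-out ignored: 40 / 120 = 33.3%. Both exceed 30%.

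**Invitations needed for 40**, rounded up:

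| Participation | No drop-out: 40 / p | With drop-out: 40 / (0.90 × p) |
|---|---|---|
| 20% | 200 | 223 |
| 25% | 160 | 178 |
| 30% | 134 | 149 |

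**Could chance close the gap?** Treat invitees as independent. At 30% participation with 10% drop-out, each invitee completes with probability 0.27, and the chance of at least 40 completers from 120 is about 7%. At 20% (probability 0.18) it is about 0.004%.

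**Sensitivity to workshop carry-over** (an assumption, not in the article). Suppose all 20 workshop experts join and 20–30% applies only to the others.
- Counted within the 120: starters 20 + 100 × 0.20 to 0.30 = 40 to 50; completers × 0.90 = 36 to 45.
- Counted on top of the 120: starters 20 + 120 × 0.20 to 0.30 = 44 to 56; completers 39.6 to 50.4.

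Forty completers require 40 / 0.90 = 44.4 starters. The number of workshop experts who must join is then:
- On top of the 120: 44.4 − 24 = 20.4 at 20% (in effect all of them), 44.4 − 30 = 14.4 at 25%, and 44.4 − 36 = 8.4 at 30%.
- Within the 120: 44.4 − 20 = 24.4 at 20% (more than the 20 available), 44.4 − 25 = 19.4 at 25%, and 44.4 − 30 = 14.4 at 30%.

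**The case against.** The strongest defence is that the panel expressly includes workshop participants, so about 20 of the 40 may be people already committed to the project. Treating them as cold invitees who join at 20–30% may be too pessimistic. If they are additional to the 120 and all join, even the lowest rate gives 39.6 completers, which is 40 for practical purposes. This stands as a possible explanation of the figure. It does not rescue the text: the article applies one pair of rates with no exemption, is silent on whether the 120 includes these experts, and says under Inclusion, exclusion and termination criteria that experts may take part in the workshop, the Delphi or both. Carry-over is therefore neither stated nor assured.

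A second defence is that 120 is approximate and the Study risks section allows more invitations. That makes a shortfall easy to remedy, and it stands. But a gap of 29 to 103 invitations (149 − 120 and 223 − 120) is more than rounding, and a contingency does not make the planned figure follow from its inputs.

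A reader might also infer that the two sections set rival invitation rules. They do not. The Study risks list is introduced as action to be taken if needed, and an approximate 120 is not a cap. Only the description of the 20–30% rate differs between the sections.

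A reader might further apply the 10% loss once per round, giving a still smaller panel. The Study risks section gives one 10% rate for the Delphi survey as a whole, so the text does not support compounding it.

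**Conclusion.** The point holds as an unreconciled set of figures. With the stated rates applied to all invitees, about 120 invitations give 24 to 36 starters and about 22 to 32 completers, not 40. Agreement with 40 depends on substantial workshop carry-over, ranging from about 9 of 20 in the most favourable case (30% participation, workshop experts additional) to all 20 or more than 20 in the least favourable, and the article states no such assumption.

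It might be inferred that the panel size of 40 is itself wrong. The document does not support that: 40 is a chosen target, not a result derived from the rates. Nor does a smaller panel invalidate the consensus rule. The rule is a percentage with no minimum panel size and no hypothesis test, so fewer experts make it coarser and less representative but leave it valid.

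The consequence is moderate and can be remedied before or during recruitment.

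**What to change.** Choose one of the following in Study phases and data collection:

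- **(a) Keep the target of 40** and plan about 149 invitations (at 30%) to 223 (at 20%). This adds 29 to 103 invitations, which the contingency under Study risks already allows. These numbers assume that the rates apply to everyone.
- **(b) Keep 120 invitations** and restate the expected panel as about 22 to 32 completers, if the rates are meant for all invitees.
- **(c) If workshop carry-over was intended**, state the participation assumed for those experts and whether they are inside or on top of the 120, and give the resulting range. With full carry-over of 20, that is 36 to 45 completers inside or about 40 to 50 on top.

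Option (b) would insert a wrong figure if carry-over was in fact assumed, so the authors should settle that first. In every case, say whether 40 counts starters or completers, and describe the 20–30% rate the same way in Study phases and data collection and in Study risks, as either the expected or a pessimistic value.

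The cost is one or two sentences, plus the extra invitations under (a).
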